**14.2 Data Management Plan**

1. The data management plan was written by the data administrator.

2. The data management plan serves as a guide for the entire data management process, and all subsequent processes should follow the time and method defined therein.

3. The contents of the data management plan include:

(1) Administration of data management plans, such as ownership, cover design, table of contents, etc.

(2) The general situation of the study, such as its purpose, overall design, etc.

(3) Data management work schedule. The schedule should reflect the start and completion time of each step in the process. The schedule should also be coordinated with the overall timetable of the entire clinical trial.

(4) Allocation of users and permissions: Includes EDC system administrators (Admin), data managers (DMs), investigators, clinical research coordinators (CRCs), clinical research associates (CRAs), etc.

(5) Data management design includes database design and logical verification design.

(6) Data processing regulations

(7) Data quality control

(8) EDC Deactivation

(9) Data security measures

(10) EDC system emergency plan

# 15. Statistical Analysis

## 15.1 Analytical Dataset

Safety set (SS): Actual data obtained from all subjects who were randomized and received 1 dose of study drug, and recorded with a security indicator. Data lacking safety values cannot be carried forward. The incidence of adverse reactions is expressed per number of cases in the SS.

Full Analysis Set (FAS): All subjects who were randomized and received 1 dose of study drug, and recorded with an efficacy indicator.

PK concentration data set: All subjects who were randomized and received 1 dose of study drug, and had at least 1 piece of blood concentration data of the study drug during the trial.

PK parameter analysis set: All subjects who were randomized and received 1 dose of study drug, and had at least 1 valid PK parameter of the study drug during the trial.

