**1.5 Preliminary Study Results**

As of July 1, 2017, a total of 25 valid subjects have been enrolled in the study. Dose escalation has reached 2.5 mg/kg, with DLT of Grade 4 neutropenia occurring in 2 cases at the dose of 2.5 mg/kg. Drug-related adverse events (≥5%) included leukopenia (14%), neutropenia (9%), decreased hemoglobin (7%) and numbness (6%). Adverse events that led to changes in medication (including dose reduction, dosing suspension and medication termination) were leukopenia, neutropenia and numbness of hands and feet. All symptoms were resolved after dose discontinuation or symptomatic treatment.

As of July 1, 2017, efficacy evaluation has been conducted on 19 subjects, among which 3 were evaluated as partial response (PR), 8 were stable disease (SD), and 8 were progressive disease (PD). The duration time for administration is up to 238 days.

Pharmacokinetic study showed that half-lives of RC48-ADC in the groups of 1.0 mg/kg, 2.0mg/kg and 2.5mg/kg were 16.2±9.5 h, 34.4±13.7 h and 49.0±27.4 h, respectively. Exposure level AUC_0-∞_ increased with dose. No anti-drug antibody was detected so far.

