**Table 4. Laboratory test items.**

| **Item Name** | **Examination Including** |
| --- | --- |
| Virology test | 5 liver function tests, HCV, and HIV |
| Routine blood test | RBC, Hb, WBC, NEUT, EO, BA, LY, and PLT |
| Blood chemistry | Myocardial zymogram (CK-MB), cTn, GGT, ALT, AST, ALP, TP, ALB,  ALB/GLO, TBIL, IBIL, ^DBIL,^ BUN, Cr, Glu, K+, Na^+^, Cl^－^, LDH, TC, TG, HDL-C, and LDL-C |
| Blood coagulation test | International Normalized Ratio (INR), prothrombin time (PT), and Activated partial thromboplastin time (APTT) |
| Routine urinalysis + urine pregnancy test | SG, pH, U-PRO, U-GLU, U-RBC, U-WBC, and HCG pregnancy test (for females during child-bearing period) |
| PK★ | Total antibody in serum, ADC and free MMAE Plasma concentration |
| Immunogenicity★ | Serum anti-ADC antibody (ADA, anti-RC48-ADC antibody) |
| Tumor markers | Specific test items will be determined by the investigators depending on the tumor type |

★ Blood samples for PK and immunogenicity assays shall be handled as per blood sample handling procedure, and then sent by the sponsor to a designated laboratory for assay.

(5) Imaging Examination

At baseline, all patients with solid tumors must undergo CT/MRI scans of the chest, abdomen and pelvis according to the RECIST v1.1. For osteopathy patients, confirmatory bone scan shall be carried out at the time of baseline. Tumor assessment will be performed by using CT/MRI/radiography.

(6) ECG: ECG (12-lead) examination will be conducted 3 times with an interval of 5 min prior to each dose.

ECG monitoring will be carried out during medication.

ECG (12-lead) examination will be conducted 3 times with an interval of 5 min within 1-2 h postdose.

(7) Efficacy Evaluation

Objective Response Rate (ORR) refers to a percentage of patients whose tumors have shrunk to a given volume and maintained for a period, it includes PR+CR (as per RECIST 1.1).

At the dose-escalation trial phase, efficacy in each patient will be evaluated after every 2 treatment cycles, wherein one treatment cycle consists of 2 doses. For patients dosed Q3W, efficacy evaluation will be conducted after every 3 treatment cycles, wherein one treatment cycle consists of 1 dose.

At the extended trial phase, efficacy evaluation will be carried out for each subject according to the following evaluation criteria every 2 treatment cycles. ORR will be calculated on the basis of result of this evaluation.

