**Evaluation Criteria**

In accordance with RECIST 1.1, objective evaluation criteria for antineoplastic drugs are established as follows:

**Complete Response (CR)** All target lesions disappear, and minor diameter of any pathological lymph node (including target and non-target nodes) shall be decrease by < 10 mm.

**Partial Response (PR)** Sum of diameters of target lesions is less than baseline level at least by 30%.

**Stable Disease (SD)** Target lesions neither shrink to a level of PR nor enlarge to a level of PD, and the minimum of sum of their diameters can serve as a reference value for the study.

**Progressive Disease (PD)** With the minimum of sum of diameters of all measured target lesions throughout the study as a reference, relative increase in sum of diameters is at least 20% (a baseline measurement will serve as the reference if it is the smallest value); in addition, absolute value of sum of diameters has to increase by at least 5 mm (occurrence of one or more new lesions is deemed PD, too).

(8) Safety and Tolerance Assessment

Body weight of each patient is to be measured prior to each treatment, which will be used in PK calculation.

When being subjected to blood pressure and pulse measurement, a subject must rest in sitting position for at least 3 min. Each measurement of blood pressure shall be taken on the same arm.

Result of 12-lead ECG will be recorded during the trial. The records include ECG date and time, heart rate, PR interval, QT interval, QTcB duration, and QRS duration. In overall evaluation, whether or not any clinically significant abnormality is found shall be defined. Clinically significant abnormalities, if any, have to be further defined. Signed original ECGs will be archived in the study site.

If laboratory test results of a patient during the screening period are out of a range specified in the protocol, then they can be reviewed once prior to enrollment. If the review result is still out of specification range, then this patient cannot be included in the trial.

If the result of a laboratory test of a patient during the screening period is out of normal range but this test is not specified in the protocol, then it will be judged by the investigators whether it is clinically significant or not. This test may be repeated once as soon as possible in a bid to eliminate laboratory error.

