## 8.3 Extended Trial

Patients evaluated as CR, PR and SD in the first efficacy evaluation during dose escalation phase can enter the extended trial on a voluntary basis, provided that investigators estimate that continuous medication would be beneficial to the patient. A time frame of ±3 days is allowed for all tests (except imaging examination) for each visit. An extended trial should include the following tests:

- ECOG evaluation;
- Body weight measurement, physical examination and vital sign examination for 1 time;
- Examine the following items before each administration: routine blood test, routine urinalysis, blood chemistry (Troponin, GGT, ALT, AST, ALP, TP, ALB, ALB/GLO, TBIL, IBIL,DBIL, BUN, Cr, Glu, K+, Na+, Cl－, LDH, TC, TG, HDL-C, and LDL-C);

On July 4, 2017, the investigators and sponsor decided to discontinue the original dose-escalation study starting with 2.0 mg/kg Q3W. Instead, a dose-escalation study with an initial dose of 1.25 mg/kg QW was added. Subjects participating in the extended trial should undergo routine blood test, routine urinalysis, blood biochemical examination before the initial administration of each treatment cycle;

- Tumor markers (specific test items will be determined by the investigators depending on the tumor type);
- ECG examination before each administration; if the subject experiences precordial chest pain, palpitations or other symptoms, or has an abnormal ECG, CK-MB test and echocardiography may be added;

On July 4, 2017, the investigators and sponsor decided to discontinue the original dose-escalation study starting with 2.0 mg/kg Q3W. Instead, a dose-escalation study with an initial dose of 1.25 mg/kg QW was added. Subjects participating in the extended trial should undergo ECG examination before the initial administration of each treatment cycle. If the subject experiences precordial chest pain, palpitations or other symptoms, or has an abnormal ECG, CK-MB test and echocardiography may be added;

- Tumor imaging examination, including CT or MRI scans of the chest, abdomen, pelvis, brain and other related lesions. For subjects rated as CR or PR at the initial evaluation, their efficacy should be verified 4 weeks later. A time frame of ±7 days is allowed. Specific evaluation time points are as follows:
  - once every 2 treatment cycles;
  - when the treatment ends or subject withdraws.

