## 15.4 Efficacy Analysis

FAS data is used for efficacy analysis.

Due to the small number of subjects and the mainly descriptive statistics, professional analysis should be performed on the results.

The number of cases, means, standard deviations, medians, minimums, and maximums are calculated for continuous variables.

Frequency and composition ratio are calculated for count and grade data.

For primary evaluation, the objective responses of subjects are evaluated in reference to the Response Evaluation Criteria in Solid Tumors (RECIST) (version 1.1). The objective response rate (the proportion of patients with confirmed complete response or partial response, according to RECIST) is calculated and described statistically.

Descriptive analysis is performed for other efficacy indicators and exploratory analysis of the relationship between pharmacokinetic parameters and efficacy is conducted.

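### The FAS drops dosed subjects with no efficacy record, which can only raise the ORR or leave it unchanged, and Sections 7 and 15.4 disagree on which subjects the ORR covers

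*Protocol*

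**What the plan says.** Section 15.1 gives the efficacy set as "Full Analysis Set (FAS): All subjects who were randomized and received 1 dose of study drug, and recorded with an efficacy indicator". Section 15.4 states "FAS data is used for efficacy analysis" and defines the ORR as "the proportion of patients with confirmed complete response or partial response, according to RECIST". It does not limit the ORR to one phase of the trial.

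Section 7, item (7), is narrower. It says "At the extended trial phase, efficacy evaluation will be carried out for each subject according to the following evaluation criteria every 2 treatment cycles", and the next sentence is "ORR will be calculated on the basis of result of this evaluation".

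The name 'Extended Trial' covers two routes. Under Section 8.3, "Patients evaluated as CR, PR and SD in the first efficacy evaluation during dose escalation phase can enter the extended trial", on a voluntary basis and if the investigator expects benefit. Under Section 8.4, at least 10 plus at least 20 new patients, grouped by HER2 status, are enrolled directly at 2.0 mg/kg Q2W. Their flow chart (Appendix 4) has its own screening column and Cycle 1, and no response condition applies.

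Two wording points bear on the same analysis. All four sets in Section 15.1 require subjects to have been randomized, although the trial is open-label dose escalation and describes no randomization. For complete response, the Evaluation Criteria in Section 7 say that the "minor diameter of any pathological lymph node (including target and non-target nodes) shall be decrease by < 10 mm".

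**The concern.** The ORR is the only efficacy rate the protocol defines, and Section 15.4 makes objective response the primary evaluation within efficacy. Its denominator should be fixed by what is known at first dose.

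The FAS instead conditions on something that happens later. The first scheduled evaluation comes after two cycles of two doses, which on Q2W is 4 × 2 = 8 weeks. The subjects have advanced disease that standard treatment has failed or cannot address. Those who die or deteriorate before any assessment are the ones least likely to have responded, and they leave the denominator. The term 'efficacy indicator' is not defined, and Section 7 places change in ECOG score within the efficacy evaluation, so who is excluded is not settled in advance.

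The second problem is that two sections give different ORR populations. If the extended phase is taken to include the roll-overs, escalation subjects with early progression are missing by rule while the responders and stable subjects from the same dose groups are present.

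**Working it through.** **Inputs** (Section 1.5, as of 1 July 2017): 25 subjects enrolled, and "efficacy evaluation has been conducted on 19 subjects, among which 3 were evaluated as partial response (PR"), with 8 SD and 8 PD. The protocol states no ORR, target rate, power or sample-size calculation for response, so the only figure to reproduce is the number evaluated: 3 + 8 + 8 = 19. It agrees.

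**Step 1: the FAS condition.** Let d be the share of dosed subjects with no efficacy record. None of them can be a responder, so

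ORR on the FAS = ORR on all dosed / (1 − d).

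Interim counts, taking all 25 enrolled as dosed (exact Clopper-Pearson 95% intervals):

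| Denominator | ORR | 95% CI |
| --- | --- | --- |
| All 25, unevaluated counted as non-response | 3/25 = 12.0% | 2.5 to 31.2 |
| 19 evaluated | 3/19 = 15.8% | 3.4 to 39.6 |

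Here d = 6/25 = 24%, and 12.0% / 0.76 = 15.8%. This is the most the condition could do on these counts: any of the six who were only awaiting a first scan would not be excluded in the final analysis.

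For other values of d (assumed; the protocol gives none), an all-dosed ORR of 20% is reported as:

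- d = 5%: 20 / 0.95 = 21.1%
- d = 10%: 20 / 0.90 = 22.2%
- d = 20%: 20 / 0.80 = 25.0%

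**Step 2: the extended-phase ORR.** Suppose all 3 PR and 8 SD subjects roll over (11) and join 30 direct enrolees with an assumed ORR p. The pooled rate is (30p + 3)/41. Restoring the 8 escalation subjects with PD gives (30p + 3)/49.

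| Assumed p | Pooled extended phase (41) | All evaluated, both phases (49) |
| --- | --- | --- |
| 12% | 16.1% | 13.5% |
| 15.8% | 18.9% | 15.8% |
| 20% | 22.0% | 18.4% |
| 30% | 29.3% | 24.5% |

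The numerators are equal, so the ratio is 49/41 = 1.20 whatever p is. If only the directly enrolled patients are counted, the selection is zero: a patient in that cohort who progresses early is already in the extended phase and counts as PD.

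**Step 3: the sections side by side.** Section 15.4 with Section 15.1 keeps escalation subjects with PD, because they have an efficacy record, and loses only those with none. Section 7 read with Section 8.3 loses the escalation PDs as well. Section 7 read with Section 8.4 alone loses neither group by an entry rule. Nothing in the protocol chooses between these readings.

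**The case against.** Several points on the other side are sound.

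- **Imaging at withdrawal.** Sections 8.2, 8.3 and 8.5 call for tumour imaging when treatment ends or the subject withdraws; 8.2 and 8.5 exempt those assessed in the preceding 4 or 3 weeks. Many subjects who stop for toxicity before the first scheduled scan would still gain a record. This stands and shrinks the bias. It does not recover subjects who die, are too ill to be scanned, or refuse.
- **Most of the extended phase is unselected.** A reader might infer that early progressors cannot enter the extended phase. That holds only for the Section 8.3 route. The at least 30 patients of Section 8.4 enter with no response condition and may well be the majority.
- **Pooling is not stated.** A reader might infer from the shared name that roll-overs and direct enrolees will be pooled. No section says so, and the protocol gives them separate sections and flow charts. The name leaves the matter open; it does not settle it.
- **A larger multiple is available but unsupported.** Taking only the 11 non-progressors gives 3/11 = 27.3%, which is 2.3 times 12.0%. The protocol never states 11 as an ORR denominator. That figure assumes that every CR, PR or SD subject rolls over and that no direct enrolee counts. Section 1.5 also does not say that the three PRs were confirmed, as Section 15.4 requires.
- **Subgroup tables and intervals.** Breakdowns by dose, schedule and HER2 stratum, and confidence intervals, commonly belong in the statistical analysis plan, to which Section 15.5 refers. Their absence here is no fault.
- **The wording slips.** It would be over-reading to say that the term 'randomized' leaves every set empty, since dosed subjects are plainly meant. The nodal wording reads like a translation error, and the protocol names RECIST 1.1 as its standard. Neither slip biases the denominator, but both are wrong as written.

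**Conclusion.** The concern holds in a limited form. The FAS condition can only leave the ORR unchanged or raise it relative to all dosed subjects. On the interim counts the rise is at most from 12.0% to 15.8%, assuming all 25 enrolled subjects were dosed and none of the six was merely awaiting a scan. The final effect cannot be computed, because the protocol does not define what counts as an efficacy record.

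Sections 7 and 15.4 give different ORR populations. An extended-phase ORR that includes roll-overs would be inflated, by a factor of about 1.2 in the illustration with 11 roll-overs and 30 direct enrolees, compared with the same subjects plus the escalation PDs. The 11 is an upper limit on roll-overs from those counts, since entry is voluntary and needs the investigator's judgment, and some of the 25 may have been enrolled directly. An ORR restricted to the Section 8.4 cohort carries no such selection. The documents therefore do not support a flat statement that the planned ORR is biased upward through entry to the extended phase.

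Severity is moderate. Efficacy is a secondary objective and the analysis is descriptive, with no hypothesis or threshold. Section 3 ties the recommended Phase II dose to the DLT-driven escalation, so no error rate or decision rule is affected.

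**What to change.** - **Section 15.1:** in all four sets, replace the condition of randomization and one dose with receipt of at least one dose. Delete the efficacy-record condition from the FAS.
- **Section 7 item (7) and Section 15.4:** give one ORR definition in both places: confirmed CR plus PR over all dosed subjects, with no post-baseline assessment counted as non-response. Show the ORR in evaluable subjects as a sensitivity analysis.
- **Extended phase:** report the directly enrolled Section 8.4 cohort separately. Count roll-over subjects only with their escalation dose group, from their first dose. Distinct names for the Section 8.3 and Section 8.4 parts would remove the ambiguity.
- **Evaluation Criteria, complete response:** reword the nodal condition as a residual short axis below 10 mm, not an amount of shrinkage, in line with the RECIST 1.1 criteria the protocol invokes.

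The cost is a wording amendment and a few table rows, with no new data to collect. The reported ORR may be somewhat lower.

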## 15.2 Safety Analysis

- Safety analysis is conducted using the SS.
- Due to the small number of subjects and the mainly descriptive statistics, professional analysis should be performed on the results.
- Qualitative indicators are described by frequency tables, percentages, or composition ratios; quantitative indicators are described by averages, standard deviations, or maximum, minimum and median.
- The incidence of adverse events and adverse reactions is calculated.
- The rate and frequency of adverse events and adverse reactions are listed by systems to calculate the percentage.
- Various adverse events are listed in detail.
- Various adverse reactions are listed in detail.
- The number of cases and rate of "conversion to abnormal" or "abnormality exacerbation" in laboratory indicators, ECG and physical examinations after the trial are recorded.
- Laboratory indicators, ECG, abnormal physical examinations and clinical interpretations are listed.
- The total incidence of adverse reactions in each group and the incidence and severity of adverse reactions in each system are investigated.
- Exploratory analysis is performed on the relationship of PK parameters with SAE and DLT.

## 15.3 Pharmacokinetic Analysis

A c-t curve is plotted for the blood concentration (c) vs time (t) for each subject listed in the PK concentration data set. In addition, a chart is made of the mean and standard deviation of the drug concentrations at various time points, and an average blood concentration curve is plotted with a standard deviation.

The noncompartmental method is used to analyze data in the PK parameter analysis set. Pharmacokinetic parameters of each subject and the mean and standard deviation of these parameters are calculated. The pharmacokinetic parameters are compared between the first and last drug administration and between different dose groups.

Pharmacokinetic properties are analyzed. The dose proportionality of C_max_ and AUC_0-∞_ after a single dose is analyzed by a power function model to evaluate the linear relationship of multiple doses.

Cmax The maximum plasma concentration observed

_T_max Time (an observation time point) at which the C_max_ is observed

Clast The last detectable plasma concentration

T_last_ Time (an observation time point) at which the C_last_ is observed

_k_el Elimination rate constant, based on a linear regression of the terminal elimination phase of the plasma concentration-time curve

T_1/2_λz The estimated terminal elimination half-life in plasma, calculated by dividing In2 by the terminal elimination rate constant (0.693/k_el_)

AUC_0-t_ The area under the plasma concentration-time curve between time 0 (before dosing) and the last time point of quantifiable detection (T_last_)

AUC_0-∞_ The area under the plasma concentration-time curve from time 0 (before dosing) extrapolated to infinity

% AUC_0-∞_ Percentage of AUC from 在AUC_0-t_ extrapolated to AUC_0-∞_

Vz/F Apparent volume of distribution in terminal elimination phase

CL/F Apparent clearance after drug administration; CL/F = dosage/AUC0-∞

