**1.3.2 Pharmacokinetics of Crab-Eating Macaques**

(1) ADC, TAb, and MMAE showed nonlinear pharmacokinetics in crab-eating macaques within the experimental dose range (2, 4 and 8 mg/kg), and the systemic clearance gradually decreased with increasing doses.

(2) After a single intravenous infusion at different doses of RC48-ADC in cynomolgus monkeys, serum concentration and pharmacokinetic parameters of ADC and TAb were similar, with no statistical difference.

(3) The TAb concentration of the nude antibody group was higher than that of the RC48-ADC group

For 4 mg/kg RC48-ADC and 4 mg/kg RC48 nude antibody + 0.08 mg/kg MMAE control group, all pharmacokinetic parameters regarding total antibody except MRT were not statistically different. The plasma concentration of the nude antibody group was higher than that of the RC48-ADC group.

(4) The MMAE exposure level of RC48-ADC was much lower than that of the combined MMAE and nude antibody group at the same dose. The systemic exposure and maximum toxic concentration of RC48-ADC were about 1/5 (18.18%) and 1/310 (0.32%) of those of the latter respectively, suggesting that the free MMAEs detached from RC48-ADC were maintained at a relatively low exposure level in crab-eating macaques' blood.

After a single intravenous injection of combined RC48 nude antibody + MMAE (4+0.08 mg/kg) in the control group, the plasma concentration peaked instantaneously. The peak concentration and plasma exposure of free MMAE after 4 mg/kg RC48-ADC administration were approximately 0.32% and 18.18% of those of the control group at the same dose. This result suggested that the cytotoxic pentapeptide MMAE conjugated to RC48-ADC was stable in the blood, and the systemic exposure of free MMAE within 14 days after a single intravenous infusion in crab-eating macaques was less than 20% of the amount of its conjugate. The maximum toxic concentration was reduced by more than 300 folds, theoretically reducing the systemic toxicity caused by MMAE.

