**3 Study Design**

It is expected to set up 9 dose groups to conduct an open-label, dose-escalation study. Patients with HER2-positive solid tumors are enrolled.

The doses are proposed to be escalated to 0.1 mg/kg, 0.5 mg/kg, 1.0 mg/kg, 1.5 mg/kg, 2.0 mg/kg, 2.5 mg/kg, 3.0 mg/kg, 3.5 mg/kg and 4.0 mg/kg.

If a dose has passed the safety observations in another Phase I clinical trial (at the Cancer Hospital, Chinese Academy of Medical Sciences), investigators and sponsors may meet to discuss and adjust the dose increment in dose escalation trial, or skip this dose and proceed directly to the next dose according to the corresponding results, in order to reduce the patient's exposure to ineffective doses.

During the trial, the dose increment and the maximum dose can be adjusted based on actual results after consultation between the investigators and sponsor.

The first dose (0.1 mg/kg) is given to 1 subject to collect pharmacokinetic data of a single dose. After safety observations, the patient can continue with trials of the following dose levels on a voluntary basis without additional collection of pharmacokinetic data (this scheme is suitable to all subsequent subjects to ensure their benefits).

The second dose (0.5 mg/kg) group enrolls another subject. Pharmacokinetic data of a single dose are collected for this patient after first dosing. Dosing interval (Q1W, Q2W or Q3W) will be determined by the investigators and sponsor based on the data obtained from the 2 patients. Q2W was tentatively selected at a meeting on Jan. 26, 2016. Q2W dosing means 1 treatment cycle includes 2 doses.

Repeated doses are given to subjects from the second dose (0.5 mg/kg) forward to collect pharmacokinetic data of repeated doses. Pharmacokinetic data are collected before and after each of 4 doses for one patient, no matter what dosing interval is used.

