**Table 1. Dosage escalation grouping.**

| **Dose** | **Number of cases** |
| --- | --- |
| 0.1 mg/kg | 1 |
| 0.5 mg/kg | 1 |
| 1.0 mg/kg | 3-6 |
| 1.5 mg/kg | 3-6 |
| 2.0 mg/kg | 3-6 |
| 2.5 mg/kg | 3-6 |
| 3.0 mg/kg | 3-6 |
| 3.5 mg/kg | 3-6 |
| 4.0 mg/kg | 3-6 |

Subjects are enrolled in the traditional 3+3 mode from 1.0 mg/kg dose group forward.

If a dose has passed the safety observations in another Phase I clinical trial (at the Cancer Hospital, Chinese Academy of Medical Sciences), investigators and sponsors may adjust the dose increment in dose escalation trial, or skip this dose and proceed directly to the next dose according to the corresponding results, in order to reduce the patient's exposure to ineffective doses.

During the trial, investigators can adjust the dose increment and maximum dosage based on the results of the trial.

On Oct. 18, 2016, investigators and sponsors met and determined an additional dose escalation study for Q3W administration. Starting from the 2.0 mg/kg dose group, 2-3 patients are enrolled. Pharmacokinetic data from Q3W administration are collected repeatedly. The dose next to 2.0 mg/kg is determined based on the results of the dose escalation study with Q2W administration.

2) The original dose-escalation study starting with 2.0 mg/kg Q3W was discontinued. Instead, dose escalation trial is carried out with an initial dose of 1.25 mg/kg, followed by 1.5 mg/kg, in the traditional 3+3 mode with QW administration. Symptomatic supportive treatment is allowed in the DLT evaluation period until MTD is reached. If the 1.5 mg/kg dose group does not reach MTD, the sponsor and investigators will jointly decide on the next escalating doses or whether to terminate the dose escalation trial.

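### Read plainly, one power-model exponent over all doses rests 40% to 65% of its slope information on the single 0.1 mg/kg subject; report the exponent for 1.0 mg/kg and above beside it

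*Protocol*

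**What the plan says.** Section 15.3 names the method for dose proportionality: Cmax and AUC0-∞ "after a single dose is analyzed by a power function model to evaluate the linear relationship of multiple doses". It gives no dose range and no check that the log-log relation is straight. Section 15.1 defines the analysis population as "PK parameter analysis set: All subjects who were randomized and received 1 dose of study drug, and had at least 1 valid PK parameter", so no dose level is left out.

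Section 3 lists the dose levels as "0.1 mg/kg, 0.5 mg/kg, 1.0 mg/kg, 1.5 mg/kg, 2.0 mg/kg, 2.5 mg/kg, 3.0 mg/kg, 3.5 mg/kg and 4.0 mg/kg". The bottom two have one subject each: "The first dose (0.1 mg/kg) is given to 1 subject to collect pharmacokinetic data of a single dose", and then "The second dose (0.5 mg/kg) group enrolls another subject". Table 1 in Section 5 gives 3 to 6 subjects at every higher dose: "Subjects are enrolled in the traditional 3+3 mode from 1.0 mg/kg dose group forward".

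Two places bear on linearity. Section 1.5 reports human half-lives at 1.0, 2.0 and 2.5 mg/kg of "16.2±9.5 h, 34.4±13.7 h and 49.0±27.4 h, respectively". Section 1.3.2 reports that in macaques "the systemic clearance gradually decreased with increasing doses". Section 1.4 treats macaques, not rats, as the relevant species.

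Section 15.5 leaves detailed methods to a statistical analysis plan, which was not available for this check.

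**The concern.** A power model regresses log exposure on log dose, and on that scale 0.1 mg/kg lies far below every other dose. With one subject there and the rest mostly between 1.0 and 4.0 mg/kg, one person holds a large part of the information on the slope.

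That person is also outside the range of interest. Section 5 wants to spare patients further dosing at 0.1 mg/kg because it is not expected to work. It expects the effective dose to exceed 1.8 mg/kg and predicts an MTD of 2 to 3.5 mg/kg. If the exponent differs between the lowest doses and the clinical range, a single pooled exponent describes neither well. The proportionality statement for the doses that matter would then be blunted.

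**Working it through.** The protocol states no precision or sample-size figure for dose proportionality, so there is none to reproduce.

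**Step 1: slope information.** Let x = ln(dose), and let Sxx be the sum of (x − mean)² over all subjects. The share of the 0.1 mg/kg subject is (ln 0.1 − mean)² / Sxx, and its leverage is that share plus 1/n. Cohort sizes come from Table 1. The extension adds at least 10 + 20 = 30 subjects at 2.0 mg/kg (Section 3), who have a full first-dose profile (Section 6). The weekly groups are at 1.25 and 1.5 mg/kg (Section 5). Every layout has one subject at 0.1 and one at 0.5 mg/kg.

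| Layout from 1.0 mg/kg upward | n | mean x | (ln 0.1 − mean)² | Sxx | Share | Leverage |
|---|---|---|---|---|---|---|
| A: 3 per cohort to 4.0 | 23 | 0.620 | 8.54 | 15.49 | 55% | 0.60 |
| B: 6 per cohort to 4.0 | 44 | 0.716 | 9.11 | 20.30 | 45% | 0.47 |
| C: ends at 2.5 (3, 3, 3, 6) | 17 | 0.341 | 6.99 | 10.78 | 65% | 0.71 |
| D: A plus 30 at 2.0 | 53 | 0.661 | 8.79 | 15.56 | 56% | 0.58 |
| E: B plus 30 at 2.0, 6 at 1.25 and 6 more at 1.5 | 86 | 0.652 | 8.73 | 22.00 | 40% | 0.41 |

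These shares need no variance assumption. A few other layouts reach 66% to 69%. The 30 extension subjects do not help, because they add subjects near the middle of the dose range and almost no spread.

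**Step 2: is one exponent plausible?** Half-life rises 49.0/16.2 = 3.0-fold over a 2.5-fold dose range. If volume is constant (an assumption), exposure goes as dose × half-life. The implied exponents are ln(2 × 34.4/16.2)/ln 2 = 2.09 from 1.0 to 2.0 mg/kg, and ln(2.5 × 49.0/16.2)/ln 2.5 = 2.21 from 1.0 to 2.5 mg/kg. Carrying 2.21 down to 0.1 mg/kg would need a half-life of 16.2 × 0.1^1.21 ≈ 1.0 h. That makes a constant exponent doubtful, but it is an extrapolation and not an observation.

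**Step 3: what pooling would do.** Assume exponent 2.2 at and above 1.0 mg/kg and 1.0 below. The pooled slope is then 2.2 − 1.2 × [sum of (x − mean)·x over the 0.1 and 0.5 mg/kg subjects] / Sxx.

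- Layout C: 2.2 − 1.2 × (6.09 + 0.72)/10.78 = 1.44.
- Layout A: 2.2 − 1.2 × (6.73 + 0.91)/15.49 = 1.61.
- Layouts B, D and E: 1.73, 1.60 and 1.78.

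**Step 4: influence of that subject's own deviation.** A one-SD deviation moves the slope by √share standard errors whatever the CV: from √0.397 = 0.63 to √0.648 = 0.80. A two-fold error in that subject's exposure moves the slope by |ln 0.1 − mean| × ln 2 / Sxx, which is 0.09 (E) to 0.17 (C).

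**Step 5: fitting from 1.0 mg/kg upward.** The largest share of any one subject falls to 4% to 19%. Sxx becomes 4.37, 8.73, 1.82, 4.57 and 11.24 for A to E. The slope SE therefore grows by √(15.49/4.37) = 1.9, 1.5, 2.4, 1.8 and 1.4. In the smallest layout (3 per cohort, ending at 2.5 mg/kg) the factor is 2.6.

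**The case against.** The strongest reply has five parts.

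- **The SAP may settle the range.** Section 15.5 defers details, and Section 15.3 does not literally say that one slope spans all doses. This is fair: the point rests on the plain reading of Sections 15.1 and 15.3, and a range limit in the SAP would answer it.
- **Rising half-life does not contradict a power model.** A reader might infer that the protocol's own data refute a straight log-log line. They do not. An exponent above 1 is what the model is built to estimate, the two implied exponents (2.09 and 2.21) nearly agree, and the protocol gives no human PK result below 1.0 mg/kg. The half-life SDs are wide and group sizes unstated, and half-life says little about Cmax.
- **Leverage is not influence.** A reader might also infer that this one subject decides the answer. Step 4 shows that a one-SD deviation moves the slope by less than one standard error, and in the Step 3 scenario the pooled exponent stays well above 1. The exposure CV is not in the protocol, so the absolute size of such a shift cannot be fixed.
- **Other outputs help.** Section 15.3 also plans individual curves and comparisons between dose groups, which show the clinical range directly. If AUC0-∞ cannot be estimated at 0.1 mg/kg, that subject drops out of the AUC fit. The lone 0.5 mg/kg subject then carries 20% to 45% in the Q2W layouts.
- **Dropping the low doses costs precision.** This stands, and it is why the all-dose fit should stay.

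**Conclusion.** The point holds as a modest improvement to a stated method. Under the plain reading, one subject at a dose outside the clinical range carries about 40% to 65% of the information on the exponent. That figure depends only on the dose levels and cohort sizes. The half-life and macaque findings make a constant exponent over a 40-fold range doubtful without proving curvature.

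The understatement (pooled 1.44 with escalation ending at 2.5 mg/kg, 1.60 to 1.78 in the layouts reaching 4.0, against 2.2 in the clinical range) rests on an assumed break at 1.0 mg/kg and on constant volume. Even then the direction of the conclusion, more than proportional exposure, survives. PK is a secondary, descriptive objective (Section 2). The MTD rests on DLT counts, and no dose decision in the protocol uses the exponent.

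**What to change.** In Section 15.3, keep the all-dose power model and add three things:

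1. Report beside it the exponent with 90% CI, for Cmax and AUC0-∞, from the cohorts with at least 3 subjects (1.0 mg/kg and above).
2. Check curvature by adding a quadratic term in log dose to the all-dose model.
3. State that any proportionality conclusion about the clinical range comes from the fit at 1.0 mg/kg and above.

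The cost is a short addition to the text, a few extra model runs, and a wider interval for the clinical-range exponent, with an SE about 1.4 to 2.4 times that of the all-dose fit. No data are discarded.
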